### Data Collection and Procedures

#### Cross-sectional component

Research assistants, referred to as local coordinators, will review the charts of hospitalized patients on a daily basis in search of cases with one of the conditions identifying severity (Appendix 2). In cases found with these diagnoses, the relevant hospital records will be reviewed for data collection following the women's hospital discharge, death or transfer to another healthcare facility. Data unavailable on the chart but of interest to the study will be obtained from the attending medical team. For each case included, data will be collected on the demographic and obstetric characteristics of the patient, the primary determinant of maternal near-miss (the first complication to occur in the chain of events leading to severe maternal morbidity), the duration of hospitalization (prior to delivery, following delivery and total time), the occurrence of indicators of maternal near-miss at any time during hospitalization, indicators of perinatal outcome and conditions of the woman at discharge from hospital.

These data will be collected on a previously coded form developed specifically for this purpose. A central database will be constructed and the data will be included by the local investigators themselves using electronic forms. The manually completed forms will be filed and made available at technical visits for the purpose of quality control.

For the electronic inclusion of data, each center will have its own restricted area on the study website where password-protected access will be granted only to cases included at that center. An overview of all the cases included in the network will be provided in the form of monthly graphs and tables containing the number of cases included by each center. In addition, the reported diagnoses will be provided by the coordinating center on the main page of the website.

In cases of near-miss, data will be collected on avoidable factors responsible for their occurrence (delays). These factors will be classified into those related to infrastructure, the patient or the healthcare professionals. Avoidable factors related to infrastructure include cases in which difficulties in obtaining supplies or medication, transportation, communication, blood components or monitoring and treatment may have led to less than ideal care. Factors related to the patient include those generated by the patient herself or her family, either by delaying seeking professional care or by refusing treatment. Factors related to the healthcare team include delays in defining the correct diagnosis and/or inappropriate management.

The degree of complexity at each hospital will be evaluated using an adapted version of the hospital complexity index developed for the WHO Global Survey project [28]. Participating institutions will provide information on a monthly basis via the website on the total number of deliveries, live births and maternal deaths that occurred the previous month. These data will be confirmed by the principal local investigator after data collection is finished.

To minimize the number of uncertainties that research assistants may face during data collection, a manual of operation was produced containing all the necessary information on how to use the internet, how to complete the written and electronic forms and how to access the database of each individual center, as well as information regarding the standardization of diagnostic definitions.

A meeting will be held with the investigators and local coordinators of each center (two individuals from each center) at the study coordinating center immediately preceding initiation of data collection in order to provide adequate training and clarify any queries regarding the data collection process and use of the website. Sometime after the initiation of data collection, a meeting of the study's Steering Committee will also be held. A second meeting will take place involving only the local investigators after data collection has finished to discuss facts related to the previous process, disclosure of partial results, scheduling of the preliminary and final analyses, agreement on papers to be written on the results and assignment of responsibility regarding execution of each item in this process.

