## Methods/Design

This study has two components: a multicenter cross-sectional study and a concurrent cohort study.

The cross-sectional study will be implemented in 27 referral obstetric units in different geographical regions of Brazil, which have already joined the initiative for building a national network for studies on maternal and reproductive health. Over a 12-month period, the principal and local investigators will carry out prospective surveillance and will collect data for the identification of maternal near-miss and non-near-miss cases, severe maternal morbidity (potentially life threatening conditions) and maternal deaths. To determine the number of collaborating centers to be included in the present study, calculation of sample size took into consideration the number of deliveries that would have to be monitored to identify cases of near-miss and maternal deaths. Previous studies have estimated a maternal near miss incidence of approximately 8 cases per 1000 deliveries [24] and a Brazilian maternal mortality ratio of 140 per 100,000 LB. Therefore, a total of approximately 75,000 deliveries would have to be monitored in order to identify around 100 maternal deaths and 600 maternal near miss cases. These numbers are believed to be sufficient to evaluate the use of the new criteria for near-miss established by the World Health Organization in 2009 [5] and to perform analysis allowing for level of complexity of health facility, age group and specific cause.

The study population will consist of all the women admitted to the participating hospitals during the study period in whom organ dysfunction is registered (maternal near-miss, Appendix 1), in whom one of the diagnoses defined as non-near-miss severe maternal morbidity is present (Appendix 2), and those who died or were transferred to another healthcare service because of their bad health condition.

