### Clinical Criteria

Acute cyanosis

Breathing rate > 40 or < 6

Oliguria unresponsive to fluids or diuretics

Loss of consciousness for ≥ 12 hours

Unconscious, no pulse/heartbeat

Jaundice concomitantly with preeclampsia

Gasping

Shock

Coagulation disorders

Cerebrovascular accident

Total paralysis

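### The daily chart search names only Appendix 2, although the study population also takes in Appendix 1 organ dysfunction, deaths and transfers, so some near-misses can be missed

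*Protocol article*

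**What the plan says.** The Methods/Design section of the protocol article gives three routes into the cross-sectional study population:

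- women "in whom organ dysfunction is registered (maternal near-miss, Appendix 1");
- women with a diagnosis listed in Appendix 2;
- "those who died or were transferred to another healthcare service because of their bad health condition".

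The Cross-sectional component under Data Collection and Procedures describes how these women are found. Coordinators will "review the charts of hospitalized patients on a daily basis in search of cases with one of the conditions identifying severity (Appendix 2"). The next sentence ties abstraction to that search: "In cases found with these diagnoses, the relevant hospital records will be reviewed for data collection following the women's hospital discharge, death or transfer". For each included case the form then records, among other items, "the occurrence of indicators of maternal near-miss at any time during hospitalization".

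The same part of the article says that institutions report monthly totals of deliveries, live births and maternal deaths through the website, and that the local investigator confirms them at the end. Under Main outcomes, near-miss requires survival of a complication arising up to 42 days postpartum, and maternal death is counted to 42 days after the pregnancy ends.

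**The concern.** The search rule is narrower than the population it is meant to find. Appendix 2 is headed as the list of non-near-miss morbidity, yet it is the only list the daily search names. Near-miss indicators are recorded only after a woman has entered through that list. A woman who meets an Appendix 1 criterion and no Appendix 2 item belongs to the population, but the written procedure gives no way to reach her.

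Two objectives are exposed. The first specific objective is the frequency of near-miss, and missed cases can only lower it. The third is the association between organ dysfunction and maternal death, analysed by odds ratios. Those need case-level data on every woman with organ dysfunction, and the direction of any bias there cannot be stated in advance.

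A second, lesser point concerns women transferred out. Whether such a woman is a near-miss or a death depends on her status up to 42 days, and the article does not say how she is classified if that status is not known.

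**Working it through.** **Step 1. Set the two rules side by side.**

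| Route into the population (Methods/Design) | Named in the daily search (Cross-sectional component)? |
|---|---|
| Appendix 1 organ dysfunction | No |
| Appendix 2 diagnosis | Yes |
| Death | No; a monthly total per institution exists |
| Transfer for severity | No |

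**Step 2. Count how far Appendix 2 contains Appendix 1.** Appendix 1 lists 11 clinical, 8 laboratory and 6 management criteria: 11 + 8 + 6 = 25. (Lactate and the PaO2/FiO2 ratio are run together in the text and are counted as two.) Four are contained by definition in an Appendix 2 item:

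- platelets below 50,000, within platelets below 100,000;
- hysterectomy for infection or haemorrhage, within hysterectomy;
- transfusion of 5 or more units, within any transfusion;
- prolonged intubation unrelated to anaesthesia, within intubation unrelated to anaesthesia.

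That leaves 25 − 4 = 21. Some of these overlap in part: the respiratory criteria with respiratory failure, and jaundice with preeclampsia where the preeclampsia is severe. Others have no direct counterpart. Examples are "Cerebrovascular accident", total paralysis, shock, oliguria, creatinine, bilirubin, lactate, pH, vasoactive drugs, dialysis and resuscitation.

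**Step 3. Allow for companion markers.** The count in step 2 is of criteria, not women. A woman with one of the 21 still enters if she also has any Appendix 2 item, such as ICU admission, central venous access, more than 7 postpartum days in hospital, any transfusion, major surgery, haemorrhage, sepsis or seizures. Many will. The documents give no figure for the remainder.

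**Step 4. Reproduce the plan's own figures.**

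- Near-misses: 75,000 × 8/1000 = 600, as stated.
- Deaths: 75,000 × 140/100,000 = 105, against around 100 stated. The ratio is per live birth; if 95% to 98% of deliveries give a live birth (assumption), the result is 99.8 to 102.9.

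The planned numbers are consistent and assume complete case finding.

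**Step 5. Give a scale for the possible loss.** With 600 events treated as Poisson, the standard error is √600 / 75,000 × 1000 = 0.327 per 1000. The 95% interval is 8 ± 1.96 × 0.327 = 7.36 to 8.64 per 1000. The half-width is 0.64, and 0.64/8 = 8%. For assumed missed shares:

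| Missed (assumed) | Found | Rate per 1000 |
|---|---|---|
| 2% | 588 | 7.84 |
| 5% | 570 | 7.60 |
| 10% | 540 | 7.20 |
| 20% | 480 | 6.40 |

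A loss above about 8% would exceed sampling error. The interval ignores clustering within the 27 centres; allowing for it would normally widen the interval and raise that threshold.

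**Step 6. If the loss differed by hospital complexity.** With a true rate ratio of 1.00, the observed ratio is (1 − share missed in low-complexity units) / (1 − share missed in high-complexity units). If 5% are missed in high-complexity units and 10% or 20% in low-complexity units (assumptions), it is 0.90/0.95 = 0.95 or 0.80/0.95 = 0.84. If both miss 10% it stays at 1.00.

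**Step 7. If deaths after transfer were counted as near-misses.** Deaths as a share of deaths plus near-misses are 105/705 = 14.9%. Moving 5 or 10 deaths (assumption) gives 100/705 = 14.2% or 95/705 = 13.5%.

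**The case against.** The strongest reply is that the article describes two stages: a broad entry search, then recording of near-miss indicators in everyone included. On that reading the Appendix 2 reference is a loose parenthesis, and the Abstract's aim of identifying all maternal complications shows the intent. Appendix 2 is also broad, and most of its markers do not need an ICU. This stands in part. It rules out the inference that women meeting any of the 21 criteria not contained in Appendix 2 are lost; only those with no Appendix 2 item at all are at risk. It does not remove the mismatch, because the article states the search rule and limits abstraction to what that rule finds.

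In-hospital deaths have a second source in the monthly totals. That also stands: an unscreened death would show as a discrepancy. But a total carries no organ-dysfunction data, and the article does not describe matching totals to cases.

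A reader might infer that under-counting is worse in less complex hospitals. No section says so. All 27 sites are referral units and none is said to lack an ICU. It is a possibility, because ICU admission depends on facilities and analysis by complexity is planned, but it is not a finding.

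A reader might also infer that follow-up ends at transfer and that transferred women are counted as survivors. The text says only when records are "reviewed for data collection following the women's hospital discharge, death or transfer to another healthcare facility". It gives no rule that codes them as alive. Tracing after transfer may be in the manual of operation or the full protocol, neither of which is shown, so its absence from the article is not itself a fault.

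**Conclusion.** The mismatch holds on the face of the document: the daily search covers one of the routes into the study population and omits the others. Followed as written, it can miss near-misses that carry no Appendix 2 item, such as an isolated stroke, paralysis, or renal or metabolic failure, and so lower the near-miss frequency.

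The size is unknown. Every missed share in the working is an assumption; the one benchmark from the plan's own figures is that a loss of about 8% of 600 would match the sampling error of the overall rate. The documents do not support saying that near-misses certainly are missed, that the loss is unequal across complexity levels, or that transferred women default to survivors. The planned 75,000 deliveries, 600 near-misses and around 100 deaths are unaffected.

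The transfer point is secondary. The outcome definitions need status to 42 days, so an explicit category for unknown outcome is a sensible safeguard.

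**What to change.** 1. In the Cross-sectional component, replace the search rule with one that matches Methods/Design: any Appendix 1 or Appendix 2 condition, any maternal death, or any transfer out for severity.
2. Match individually abstracted deaths to the monthly institutional totals, and abstract any death that the search did not find.
3. State that a woman transferred out whose vital status to 42 days is unknown is classified as outcome unknown, not as a survivor, in the organ-dysfunction and death odds ratios.

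The first change is one sentence and a longer checklist for coordinators who already read charts daily; the cost is slightly more chart time. The second uses totals already collected. The third needs no new data. If the sponsor also wants to trace women after transfer, that should be checked against the consent waiver under Ethical aspects, which rests on chart data without identification of the woman. The search rule should be settled before data collection starts, because women never abstracted may be hard to recover later.

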#### Longitudinal component

As in the cross-sectional component, women with one of the conditions indicative of severity will be selected as potential subjects for longitudinal evaluation. Once identified, research assistants who are not involved in the cross-sectional portion of the study will invite eligible women to participate in the longitudinal evaluation of the study. Women who agree to take part will be asked to sign an informed consent form and two CATI (computer assisted telephone interview) will be scheduled for 3 and 6 months postpartum plus a medical visit with the woman and the newborn infant six months following delivery.

For the control group, all women admitted to the hospital for obstetric care in the same facility on the same day on which a case has been identified and who have none of the conditions indicating severity will be eligible. Following a process of randomized selection balanced according to mode of delivery, maternal age and gestational age at the time of delivery, women in the control group will be invited to participate in the study by the research assistants in the same way as candidates to the study group. Three months after delivery, the study call center will contact the women to carry out the first step in data collection. At the time of this contact, the interviewers will again go over the objectives of the study and will apply standard questionnaires designed to investigate quality of life and postpartum depression. This interview is estimated to last around 20 minutes.

At six months postpartum, the study call center will contact the women again to carry out the second step in data collection. At this contact, the interviewers will go over the study objectives once again and apply the same standard questionnaires on quality of life and postpartum depression, lasting no more than 20 minutes. In the case of women who do not have a telephone, a reminder letter will be sent asking them to phone the study call center at the sixth month postpartum to enable the interview to take place.

At the end of the 6-month telephone interview, the interviewer will confirm the date, time and place of the visit that was previously scheduled when the women were still in hospital. The women will be reminded that they should bring the baby to the visit. Even if they do not authorize the participation of their infants in the study, the women will be invited to return to the hospital and answer the questionnaires. The interview will be carried out by a trained female interviewer, who will apply standard questionnaires to evaluate posttraumatic stress disorder, sexual function and the woman's perception of her functional status in routine activities, taking no more than 35 minutes for each woman. After the mothers have answered the questionnaires, the weight, height and neuro-psychomotor development of the infants will be evaluated by a specially trained pediatrician, taking around 20 minutes. Finally, the women will receive a token cash payment as a contribution towards their transportation and food costs while attending this visit.

The following instruments will be used for data collection:

#### Posttraumatic Stress Disorder (PTSD) Checklist - Civilian Version (PCL-C)

This questionnaire has been validated in Brazil to screen for the diagnosis of posttraumatic stress disorder. It contains 17 items in which women will indicate to what extent she has been disturbed by symptoms over the past month on a scale of 1-5 (ranging from not at all to a lot). A score ≥ 3 (a medium score) for any one of the items is considered indicative of a clinically significant symptom.

#### Medical Outcomes Study 36-Item Short-Form Health Survey (SF36)

This is a generic questionnaire for evaluating quality of life that has been validated for use in Brazil. It is multidimensional with 36 items in 8 scales: physical functioning, role-physical, body pain, general health, vitality, social functioning, role-emotional and mental health. Final scores vary from 0 to 100 (poorest to best).

#### Female Sexual Function Index

A multidimensional questionnaire used to evaluate female sexual function consisting of 19 questions in 6 domains: desire, arousal, lubrication, orgasm, satisfaction and pain. Final scores vary from 2 to 36, a cut-off point < 26 having been proposed as determinant of sexual dysfunction. This questionnaire has been culturally adapted for use in Brazil.

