### Main hypotheses

In survivors of severe acute maternal morbidity:

• health and quality of life would be poorer;

• posttraumatic stress would be more common;

• postpartum depression would be more common;

• sexual function would have deteriorated and the woman's return to sexual activity would take longer;

• functional status in routine activities would be evaluated as poorer.

In the children born from a pregnancy associated with severe maternal morbidity:

• immediate perinatal outcome would be poorer;

• the occurrence of impaired neuromotor and weight-height development would be significantly higher.

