#### Return to sexual activity

Time taken by the woman to recommence sexual activity after delivery and reason given for not recommencing sexual activity.

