### Data analysis

Data analysis will be performed in sub-groups according to the time of occurrence of the near-miss or severe maternal morbidity (in adolescence, older ages or at another time in the woman's reproductive life) and determining cause (hypertension, hemorrhage, abortion or other causes). The rates of maternal near-miss will be calculated for each collaborating center using the WHO maternal near miss approach [5], and frequencies of non-near-miss severe maternal morbidity will be calculated using specific defined diagnoses. General estimates will be calculated together with their respective 95% confidence intervals. The association between organ dysfunction and maternal death will be estimated using odds ratios, likelihood ratio test and their respective 95% confidence intervals. In addition, relative risks will be calculated for sexual dysfunction, postpartum depression, posttraumatic stress disorder, deterioration in quality of life, deterioration in the woman's perception of her own functional status in routine activities, risk of adverse perinatal outcome and risk of impaired neuromotor and weight-height development in the children born from the pregnancy associated with severe maternal morbidity.

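### The FSFI < 26 relative risk at six months does not separate women who have not resumed sexual activity from women with impaired function

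*Protocol article*

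**What the plan says.** All places are in the Protocol article.

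- **Timing and recipients.** Under Longitudinal component, the FSFI belongs to the "medical visit with the woman and the newborn infant six months following delivery". A trained interviewer attends, "who will apply standard questionnaires to evaluate posttraumatic stress disorder, sexual function and the woman's perception of her functional status in routine activities". No restriction to sexually active women is written.
- **Instrument.** Under Female Sexual Function Index, it has "19 questions in 6 domains: desire, arousal, lubrication, orgasm, satisfaction and pain". The same section adds: "Final scores vary from 2 to 36, a cut-off point < 26 having been proposed as determinant of sexual dysfunction". No other criterion for dysfunction is given.
- **Analysis.** Under Data analysis, "relative risks will be calculated for sexual dysfunction, postpartum depression, posttraumatic stress disorder" and other outcomes. No denominator is named for sexual dysfunction.
- **Hypothesis.** Main hypotheses expects that in survivors "sexual function would have deteriorated and the woman's return to sexual activity would take longer".
- **Separate outcome.** Return to sexual activity is defined as "Time taken by the woman to recommence sexual activity after delivery and reason given for not recommencing sexual activity".

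The article does not say how a woman who has not resumed is scored on the FSFI, or whether she is classified or left out.

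**The concern.** Arousal, lubrication, orgasm and pain are hard to rate without sexual activity. If a woman who has not resumed is scored zero on such domains, she falls below 26 whatever her underlying function, and the dysfunction endpoint takes in the return-to-activity endpoint. This includes non-return for reasons unrelated to sexual response.

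The authors evidently expect some women not to have resumed, because they record the reason. They also expect cases to resume later. Appendix 2 defines cases partly by hysterectomy, return to the operating room, major surgery, ICU admission and long stay. These are plausible reasons for delay, and balancing controls on mode of delivery, maternal age and gestational age does not remove them. Any artefact would therefore tend to run in the direction of the hypothesis and look like confirmation. The reader of the relative risk could not tell impaired function from not having resumed.

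**Working it through.** The article gives no rate, sample size or power for sexual dysfunction, so there is no figure of the plan's own to reproduce.

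**Step 1: can a woman with zero-scored domains reach 26?**

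Inputs from the article: six domains, maximum total 36, cut-off < 26. Assumption: equal domain weights, so 36 / 6 = 6 per domain.

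Maximum total with k domains at zero = 36 − 6k:

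| Domains at zero | Maximum total | Below 26? |
|---|---|---|
| 1 | 30 | not necessarily |
| 2 | 24 | always |
| 4 (arousal, lubrication, orgasm, pain) | 12 | always |

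The stated minimum of 2 over six domains averages 2 / 6 = 0.33 per domain. That fits some domains having a floor of zero, but it also fits six small non-zero floors of 1/3 each. Zero-scoring is therefore an inference.

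**Step 2: what happens to the relative risk?**

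Assumed inputs, none given in the article:

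- d: share with FSFI < 26 among active women, equal in both groups, so the relative risk among active women is 1.00 by construction
- q1, q0: shares of cases and controls not active at six months, all classed below 26

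Share classed dysfunctional = q + (1 − q) × d.

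RR (all women) = [q1 + (1 − q1)d] / [q0 + (1 − q0)d].

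With d = 30%:

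- 15% vs 8% inactive: 0.15 + 0.85 × 0.30 = 0.405; 0.08 + 0.92 × 0.30 = 0.356; RR = 0.405 / 0.356 = 1.14.
- 25% vs 10% inactive: 0.25 + 0.75 × 0.30 = 0.475; 0.10 + 0.90 × 0.30 = 0.370; RR = 0.475 / 0.370 = 1.28.
- 10% vs 10% inactive: 0.370 in both groups; RR = 1.00. The reported prevalence is still 37% instead of 30%.

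Sensitivity, for d of 20%, 30%, 40% and 50% and inactivity in cases vs controls of 5% vs 2%, 10% vs 5%, 15% vs 5%, 20% vs 10% and 30% vs 10%:

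- lowest RR 1.03 (d = 50%, 5% vs 2%: 0.525 / 0.510)
- highest RR 1.57 (d = 20%, 30% vs 10%: 0.440 / 0.280)

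These limits belong to the pairs listed. A wider gap in inactivity gives a larger ratio, and a gap of zero gives 1.00.

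**The case against.** **A reader might infer that the plan counts every abstinent woman as dysfunctional and so guarantees a relative risk above 1.** The article does not support this. It reports that a cut-off has been proposed, gives the questionnaire at a visit and plans a relative risk. It states no scoring rule for inactive women and no analysis set. Zero-scoring is only consistent with the range. The hypothesis is that return takes longer, not that more cases will still be inactive at six months, which is the only time the FSFI is given. If both groups have resumed equally by then, there is no artefact in the ratio under equal function.

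**Scoring rules may sit in the full protocol or analysis plan.** This is fair for item-level scoring. It is weaker for the question of whether not having resumed counts as dysfunction. That decides what the announced relative risk measures, and the article itself gives the sole criterion and lists return as a distinct outcome.

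**Restricting to active women is not neutral.** This stands. Resumption comes after the exposure and is hypothesised to depend on it. Women who abstain because of pain or lost desire would drop out of an active-only analysis. If all non-resumption reflected dysfunction, the 25% vs 10% example would make 1.28 the real effect, and an active-only analysis would report 1.00. So neither analysis is sufficient alone.

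**The data to separate the two are already planned.** This is correct, and it makes the problem cheap to solve. It does not say which comparison will be reported.

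**Conclusion.** The point holds in a limited form. Followed as written, the six-month FSFI relative risk can mix non-resumption with impaired function, because no activity restriction is stated, < 26 is the only criterion and no denominator is named.

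The size is conditional. It requires inactive women to score zero on at least two domains under equal weights, and more cases than controls to be inactive at six months. Under those conditions the ratio is, for example, 1.14 or 1.28 with no difference among active women, and 1.03 to 1.57 over the listed sensitivity values. All inactivity and dysfunction rates are assumed. The mechanism is secure; its magnitude in this cohort is unknown and could be nil.

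It does not follow that the plan must produce a spurious excess, or that the active-only ratio is the true effect. The value of 1.00 among active women is built into the model, which treats non-resumption as unrelated to function.

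**What to change.** In the outcome definition, place every woman seen at six months in one of three groups:

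1. active, FSFI of 26 or more
2. active, FSFI below 26
3. not resumed, with the reason recorded under Return to sexual activity

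Then report three labelled comparisons of cases with controls, side by side:

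- the relative risk of FSFI < 26 among active women
- non-resumption, with reasons, among all women
- the all-women result, with groups 2 and 3 combined and named as such

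**Cost.** A few sentences and no new variable, since resumption and the reason are already listed as an outcome. The article does not say at which contact they are asked, so the text should state that they are recorded as of the six-month visit, and how a woman who resumed and then stopped is grouped.

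**Downside.** The active-only estimate has a smaller denominator and conditions on a post-exposure variable, so it may be biased towards the null and must not be read alone. Reporting the reasons beside it lets the reader see how much non-resumption is itself related to pain or lost desire.
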